## Abstract

**Background:**

Dementia is a growing public health concern, disproportionately affecting low- and middle-income countries. Caregivers of people living with dementia often face significant physical, psychological, social, and financial burdens, with high prevalence rates of caregiver strain in Malaysia. Mobile health (mHealth) apps have demonstrated potential to enhance caregivers’ knowledge, attitudes, and practices (KAP) and to reduce burden. However, few culturally tailored solutions exist for Malaysia. The *DemensiaKITA* app was developed to provide locally relevant information, support services, and stress management tools for dementia caregivers.

**Objective:**

The purpose of this single-blinded, nonrandomized controlled trial (NRCT) is to evaluate the effectiveness of the *DemensiaKITA* mHealth app in improving caregivers’ KAP and reducing caregiver burden in Selangor and Kuala Lumpur, Malaysia.

**Methods:**

This research will be conducted in 2 phases. Phase 1 involves the adaptation, translation, and validation of 4 instruments: Dementia Knowledge Assessment Tool Version 2, Dementia Attitudes Scale, Caregiver Task Inventory—25 items, and Short-form Zarit Burden Interview—12 items. Content, face, and construct validity, along with reliability (Cronbach α and test-retest intraclass correlation), will be established. Phase 2 is a single-blinded NRCT conducted in 4 public hospitals. A total of 100 caregivers will be recruited. Two intervention hospitals will receive the *DemensiaKITA* app, while 2 control hospitals will receive usual care (Ministry of Health dementia leaflets and video). The primary outcomes (KAP) and secondary outcome (burden level) will be assessed at baseline, 1 month, and 3 months using the validated questionnaires on an intention-to-treat basis. Data will be analyzed with descriptive statistics, chi-square and *t* tests, and generalized estimating equations.

**Results:**

Recruitment and baseline data collection are underway. Recruitment for Phase 1 (instrument validation) occurred from December 2024 until July 2025. It is expected to produce valid and reliable Malay versions of KAP and burden instruments. Recruitment for the Phase 2 NRCT will occur from August 2025 until February 2026. The first follow-up data collection for Phase 2 will occur 1 month after baseline, and the second and final follow-up will occur at 3 months. Data analysis has not yet begun. Phase 2 is expected to show significant improvements in dementia KAP and reduced caregiver burden in the intervention group compared to controls. This study was conducted without any specific external financial support or grants from any public, commercial, or not-for-profit funding agencies. The study findings are expected to be published in December 2026.

**Conclusions:**

This article describes the protocol for a single-blinded NRCT examining a novel mHealth intervention. The *DemensiaKITA* app has the potential to empower caregivers, enhance dementia care practices, and alleviate caregiver burden in Malaysia and may serve as a model for other low- and middle-income countries globally.

## Introduction

Dementia is a progressive syndrome associated with cognitive decline and behavioral and psychological symptoms, requiring substantial support from caregivers [1]. In 2018, an estimated 50 million people were living with dementia globally, with 60% residing in low- and middle-income countries [2]. In Malaysia, the prevalence of dementia among older adults is 8.5% [1,3].

Caregivers often experience significant physical, emotional, social, and financial strain [1,2,4,5], exacerbated in low-income countries where formal support services for people living with dementia remain limited [3,6]. Caregiver burden is highly prevalent, with global estimates at 49.26% and Malaysian estimates reaching 69.4% [7,8]. Additionally, a longitudinal study in Sydney, Australia, demonstrated an increase in caregiver burden from 47.4% at baseline to 56.8% after 3 years [9].

Research consistently shows substantial gaps in dementia knowledge and variable attitudes among caregivers. A survey in China reported low knowledge despite moderate attitudes [10], while a study in India found that many caregivers had only average or below-average knowledge, low to moderate attitudes, and predominantly poor caregiving practices. Evidence indicates these gaps can be improved through targeted interventions. For example, a randomized controlled trial in eastern Taiwan showed that mobile eLearning significantly enhanced dementia knowledge, attitudes, and care competency among home care workers [11]. Positive attitudes have also been associated with better caregiving practices, highlighting the value of interventions that strengthen both knowledge and attitudes through communication training, safe care techniques, behavioral management strategies, psychological support, and information on available services [10].

The rapid expansion of internet access has enabled the use of mobile health (mHealth) apps to support caregivers [3]. Prior studies demonstrate that mHealth tools can provide health information, connect users with local services, and reduce caregiver burden [5,12-14]. However, most dementia-focused apps are developed in high-income countries and predominantly in English, limiting their applicability in diverse cultural contexts [12,15,16]. More rigorous evaluations are also needed to determine how mHealth interventions influence caregivers’ knowledge, attitudes, and practices (KAP) and burden level [10,17-19].

*DemensiaKITA* is a Malaysian mHealth prototype developed to address this gap. The app provides information on dementia, caregiving strategies, management of behavioral symptoms, stress-reduction techniques, and access to local health and community resources. Its content is culturally tailored and delivered in Malay, developed collaboratively by dementia care experts and technology researchers [12]. However, its effectiveness in improving caregivers’ KAP and reducing burden has not yet been evaluated.

This study aims to (1) adapt, translate, and validate Malay-language questionnaires assessing dementia caregivers’ KAP and burden, and (2) evaluate the effectiveness of the *DemensiaKITA* mHealth app in improving KAP and reducing caregiver burden among dementia caregivers in Selangor and Kuala Lumpur through a nonrandomized controlled trial.

## Methods

### Study Design

This study consists of 2 sequential phases: (1) adaptation, translation, and validation of KAP and burden-related instruments, and (2) evaluation of the *DemensiaKITA* mHealth intervention via a single-blinded NRCT. The NRCT design was selected due to operational and ethical constraints within participating hospitals. Caregivers are tied to specific clinics based on people living with dementia follow-up, and redistributing them across hospitals for randomization would disrupt continuity of care. Cluster randomization was not feasible due to small eligible populations within each site. Individual randomization within the same clinic would introduce high contamination risks, as caregivers frequently interact and could share intervention materials.

To mitigate potential biases inherent in nonrandom allocation, the study incorporates several methodological safeguards: (1) standardized inclusion and exclusion criteria across all sites; (2) selection of hospitals with comparable geriatric services; (3) baseline comparison of groups; and (4) longitudinal analyses using generalized estimating equations (GEE) to adjust for baseline imbalances and repeated measurements [20,21]. This pragmatic design reflects real-world implementation conditions while preserving internal validity.

### Study Population

The target population is dementia caregivers in Malaysia, while the accessible study population comprises primary caregivers of people living with dementia aged 18 years and older in Selangor. The sampling population is caregivers of registered people living with dementia attending the study sites from December 2024 to February 2026. The sampling unit is a consenting primary caregiver providing direct care to registered people living with dementia.

### Phase 1: Instrument Adaptation, Translation, and Validation

#### Overview

Phase 1 involves adapting, translating, and validating 4 instruments into the Malay language: Dementia Knowledge Assessment Tool Version 2 (DKAT-2) [22], Dementia Attitudes Scale (DAS) [23], Caregiver Task Inventory—25 items (CTI-25) [24,25], and the Short-form Zarit Burden Interview—12 items (ZBI-12) [26-28]. It is scheduled from December 2024 to July 2025.

There will be forward and backward translations of the questionnaires by two independent translators. Two independent translators will translate the original questionnaires into Malay and then back into the original language. This process helps identify and rectify any discrepancies or inconsistencies in meaning. The drafted Malay versions of the KAP questionnaires will be rigorously validated, encompassing content validation, face validation, construct validation, and an assessment of reliability (Figure 1). Eligibility criteria for Phase 1 are given in Textbox 1.

**Figure 1. F1:**
[figure not shown]
Study flow chart for Phase 1: adaptation, translation, and validation. CTI-25: Caregiver Task Inventory—25 items; CVR: content validity ratio; DAS: Dementia Attitudes Scale; DKAT-2: Dementia Knowledge Assessment Tool Version 2; EFA: exploratory factor analysis; HKL: Hospital Kuala Lumpur; ICC: intraclass correlation coefficient; I-CVI: item-level content validity index; I-FVI: item-level face validity index; KAP: knowledge, attitudes, and practices; KMO: Kaiser-Meyer-Olkin; S-CVI: scale-level content validity index; S-FVI: scale-level face validity index; UMMC: Universiti Malaya Medical Center; ZBI-12: Short-form Zarit Burden Interview—12 items.

Textbox 1.The inclusion and exclusion criteria for Phase 1.
**Inclusion criteria**
A primary caregiver of people living with dementia (a person who has helped in the personal care of a person living with dementia for 1 mo or more during the last 12 mo)Aged 18 years or olderCares for older adult aged 60 years or older with any form and severity of dementiaInformal and unpaid caregiversMinimum of at least 4 h of care per day
**Exclusion criteria**
A person who is unable to communicate independently in Bahasa MalaysiaDomestic helper

#### Content Validity

Content validity will be evaluated by a panel of 6 experts comprising public health physicians, geriatricians, and 1 informal caregiver of people living with dementia who will serve as an experiential expert to ensure contextual and practical relevance for the target population. Each panel member will independently assess all the items for relevance, clarity, simplicity, and the absence of ambiguity, following established content-validity assessment procedures [29-32]. The ratings provided will be used to compute item-level and scale-level content validity indices (CVIs).

#### Face Validity

Face validity will be examined among 30 dementia caregivers who will assess the clarity and comprehensibility of each item. Their feedback will be used to calculate the face validity index in accordance with recommended guidelines [33-35]. This process will ensure that the instrument is clear and understandable to the target population.

#### Construct Validity

Construct validity will be assessed using exploratory factor analysis (EFA). Based on the recommended participant-to-item ratio of at least 5:1, a minimum of 330 participants is required, with an additional 10% to account for potential attrition, yielding a total target sample of 363 participants. EFA will be performed to evaluate the underlying factor structure and to determine whether the items load appropriately onto the intended domains [36,37]. Participants will be recruited through convenience sampling from the Geriatric Clinic at Universiti Malaya Medical Center (UMMC), Kuala Lumpur, and Hospital Kuala Lumpur. This sample size is expected to provide adequate power and stability for robust factor extraction and model interpretation.

#### Reliability

Reliability will be assessed through internal consistency and test-retest procedures. Internal consistency will be evaluated using Cronbach α for each domain and for the overall scale. Test-retest reliability will be examined over a 2-week interval using intraclass correlation coefficient, following established guidelines for reliability assessment [38-41]. This combined approach will ensure stability and consistency of the instrument across time.

### Phase 2: Effectiveness of the *DemensiaKITA* mHealth App

#### Overview

In Phase 2, the research assesses the effectiveness of the *DemensiaKITA* mHealth app intervention among dementia caregivers in Selangor, Malaysia. This phase uses an NRCT with 2 parallel arms (intervention and control) and a 1:1 allocation ratio. The study includes 3 assessment points: baseline (T0), 1 month (T1), and 3 months (T2). The intervention period spans from August 2025 to February 2026. Participants will be blinded to group allocation (single-blinded). Hospital-level allocation is applied to minimize contamination (Figure 2). Eligibility criteria for Phase 2 are given in Textbox 2.

**Figure 2. F2:**
[figure not shown]
Study flowchart for Phase 2: effectiveness trial (nonrandomized controlled trial). CTI-25: Caregiver Task Inventory—25 items; DAS: Dementia Attitude Scale; DKAT-2: Dementia Knowledge Assessment Tool Version 2; GEE: generalized estimating equations; HASA: Hospital Al-Sultan Abdullah; HTAR: Hospital Tengku Ampuan Rahimah; MOH: Ministry of Health; UiTM: Universiti Teknologi MARA; ZBI-12: Short-form Zarit Burden Interview—12 items.

Textbox 2.Inclusion and exclusion criteria for Phase 2.
**Inclusion criteria**
Primary caregiver of people living with dementia who has provided personal care for 1 month or moreAged 18 years or olderCaring for an older adult aged 60 years or older with any type of dementiaInformal and unpaid caregiverMinimum of at least 4 hours of care per dayPossesses an operational Android smartphone with mobile dataAble to use basic smartphone functions and apps
**Exclusion criteria**
Unable to communicate independently in Bahasa MalaysiaNot an Android smartphone userEmployed domestic helper

#### Study Settings

The trial will be conducted in the geriatric clinics of 4 public hospitals in Selangor, Malaysia: (1) Hospital Tengku Ampuan Rahimah, Klang; (2) Hospital Sungai Buloh; (3) Hospital Selayang; (4) Hospital Al-Sultan Abdullah, Universiti Teknologi MARA (UiTM) Puncak Alam. These settings were chosen due to their established geriatric subspecialty services and continuous caseload of dementia caregivers. To prevent contamination, hospitals were allocated based on geographic distribution and patient-flow patterns—Intervention arm: Hospital Tengku Ampuan Rahimah, Klang, and Hospital Al-Sultan Abdullah, UiTM Puncak Alam; Control arm: Hospital Selayang and Hospital Sungai Buloh (Figure 2).

Because follow-up care rarely overlaps across hospitals, this site-based allocation minimizes cross-exposure. The *DemensiaKITA* app was installed only by the research team on participants’ smartphones in the intervention arm. Caregivers were advised not to share the app or its contents during the study period.

#### Recruitment Strategy

Participants will be identified using purposive sampling among caregivers of registered people living with dementia attending the 4 participating geriatric clinics. Screening and recruitment will be conducted by the research team. Eligible caregivers will receive a full explanation of the study objectives, procedures, confidentiality safeguards, and follow-up requirements.

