#### Allocation and Blinding

Because hospitals were preassigned to their respective study arms, no individual-level randomization will be implemented. The study will be conducted as a single-blinded trial whereby participants will not be informed of their allocation to either the intervention or control group and will instead be informed that they will receive “health education material,” as stated in the patient information sheet. In addition, researchers responsible for data analysis will remain blinded to group assignment until all data have been cleaned and finalized to minimize analysis-related bias.

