#### Intervention (Intervention Arm)

Participants assigned to the intervention hospitals will receive the *DemensiaKITA* mHealth app. The app will be installed directly by the research team to prevent unauthorized sharing. Participants may access the app freely during the study period.

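### Recruiters who can be taken to know the arm choose caregivers purposively and, separately, participant blinding conceals at most the group name; both limit internal validity

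*Protocol article*

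**What the plan says.** **Allocation and recruitment.** Study Settings names two intervention and two control hospitals. Allocation and Blinding confirms: "Because hospitals were preassigned to their respective study arms, no individual-level randomization will be implemented". Under Recruitment Strategy, "Screening and recruitment will be conducted by the research team", and the method is purposive: "Participants will be identified using purposive sampling among caregivers of registered people living with dementia attending the 4 participating geriatric clinics". The section on the intervention arm adds: "The app will be installed directly by the research team to prevent unauthorized sharing".

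**Blinding.** The Phase 2 Overview states: "Participants will be blinded to group allocation (single-blinded". Allocation and Blinding explains how: the arm is not named, and everyone is told only that they will get educational material. Data analysts "will remain blinded to group assignment until all data have been cleaned and finalized". No other staff are described as blinded.

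**What participants are told and see.** "Eligible caregivers will receive a full explanation of the study objectives, procedures, confidentiality safeguards, and follow-up requirements". In the app arm, Engagement and Adherence Monitoring provides an orientation to the app's features and scheduled reminders to keep using it. Data Collection Method and Study Tool adds checks on app use and two weeks of access before the study starts. Study Settings reports: "Caregivers were advised not to share the app or its contents during the study period".

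**Safeguards and stated limits.** Study Design lists common eligibility criteria, comparable hospitals, a baseline comparison and adjusted generalized estimating equations (GEE). Inferential and Longitudinal Analysis names the covariates: age, sex, relationship, caregiving duration and the outcome's baseline score. Strengths and Limitations accepts that selection bias may arise, but gives generalizability as what it could affect. It also presents purposive sampling as adding practical relevance.

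**The concern.** Two separate mechanisms are involved.

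The first is selection. If the arm is known before a caregiver is approached, and the approach is discretionary, the kind of caregiver enrolled can differ between arms in ways that affect later scores. That biases the between-arm comparison itself, not only how far the result carries to other caregivers.

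The second is knowledge of treatment. Outcomes come from self-administered questionnaires. If caregivers know they hold the product under test, expectation can affect how they rate themselves. A reader who sees a single-blind label will assume that this route is closed.

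Only the second mechanism bears on the blinding label; the first would remain even if participants were perfectly masked.

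**Working it through.** The point disputes no stated figure. It rests mainly on reading sections of the Protocol article together.

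**Step 1: do recruiters know the arm?** The hospital fixes the arm (Study Settings; Allocation and Blinding). The research team recruits (Recruitment Strategy) and installs the app at intervention hospitals (Intervention). Among staff, only analysts are masked. No sentence says that recruiters know the arm; it is an inference, but a firm one.

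**Step 2: do they have discretion?** Textbox 2 sets who is eligible. Purposive sampling leaves open who among the eligible is approached, and the article gives no rule for that choice.

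**Step 3: what do the safeguards cover?** Adjustment acts on the five listed covariates and on whatever the baseline score carries. Motivation is not measured. The Discussion itself says that dementia severity and access to technology may influence the app's effectiveness; neither is in the covariate list. The selection bias is reduced, not removed.

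**Step 4: what is concealed from participants?**

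| Concealed | Open to the caregiver |
|---|---|
| Name of the assigned group | Study objectives, explained in full; the article's stated aim is to evaluate this app |
| | App arm: app on own phone, orientation, reminders and use checks, advice not to share |

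At most the label is concealed.

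**Step 5: which outcomes are exposed?** Attitude (Dementia Attitudes Scale), practice (Caregiver Task Inventory) and burden (Zarit Burden Interview) are self-ratings. Knowledge (DKAT-2) is marked correct or incorrect, with don't-know answers counted as incorrect, so expectation has less room to act. Selection can affect all four.

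**Step 6: scale, under assumption only.** The plan's own figure reproduces first: (2.53² + 2.76²)(1.96 + 0.842)² / 1.69² = 38.5, hence 39 per group. The average SD is √[(2.53² + 2.76²)/2] = 2.65.

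For a bias of f SDs with no true effect and n per arm, the shift in the test statistic is f√(n/2). The chance of a significant two-sided 5% result is Φ(f√(n/2) − 1.96) + Φ(−f√(n/2) − 1.96). The document gives no value of f, so a range is shown.

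| Assumed f | Knowledge points (f × 2.65) | n = 39 | n = 50 |
|---|---|---|---|
| 0 | 0 | 0.05 | 0.05 |
| 0.1 | 0.26 | 0.07 | 0.08 |
| 0.2 | 0.53 | 0.14 | 0.17 |
| 0.3 | 0.79 | 0.26 | 0.32 |
| 0.5 | 1.32 | 0.60 | 0.71 |

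For f = 0.2 and n = 39: 0.2 × √19.5 = 0.88, and Φ(−1.08) + Φ(−2.84) ≈ 0.14. The table shows why bias matters at this sample size. It does not show that bias of any given size will occur.

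**The case against.** **Selection is disclosed and partly handled.** The article lists safeguards, mentions selection bias and purposive sampling among its limitations, and adjusts for baseline score, which can take out part of the bias. Textbox 2 requires every participant, controls included, to own an Android phone and manage basic apps. This stands. A reader might infer that recruiters can freely favour app-literate caregivers in one arm; the shared criteria limit that. Nothing says that caregivers are chosen on motivation. What remains is the undefined choice among eligible caregivers and its unmeasured part.

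**Blinding is defined.** What is withheld is the group name. Controls receive leaflets and a video, explained in detail to give comparable engagement, so someone holding an app need not be certain that it is the test product. How much the explanation of objectives reveals depends on an information sheet that is not shown. This softens the point, but a full explanation of objectives and app-specific contacts sit badly with a plain statement that participants are blinded.

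**Other stronger readings that the document does not support.**
- That the same team explains the leaflets: the comparator section does not say who does.
- That all four outcomes are equally open to reporting bias: the knowledge test is scored.
- That both biases favour the app: plausible, but not shown.
- That consecutive recruitment is known to be feasible. With an equal split, 50/2 = 25 caregivers per hospital over seven months (August to February) is 25/7 ≈ 3.6 a month. If the three-month follow-up must fall in the same window, it is 25/4 ≈ 6 a month. These are rates needed; the caseload is not given, Study Design cites small eligible populations, and the Discussion expects recruitment to be difficult.

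**Analyst masking is a strength.** The link function and working correlation may be fixed in an analysis plan that is not shown. Extending the masking is therefore an improvement, not the correction of an error.

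**Conclusion.** The concern holds in two limited parts. First, purposive recruitment by staff who can be taken to know the arm leaves a selection bias that the planned criteria and covariates reduce but cannot fully remove. The limitations section is wrong to confine its consequence to generalizability. Second, the participant-blinding claim covers at most the group name, and the limitations section does not mention the visible treatment. This second weakness bears chiefly on attitude, practice and burden.

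Neither the size nor the direction of bias can be estimated from the document. A reader might take 0.2 SD, about 31% of the planned difference (0.53/1.69), as the expected bias; that input is an assumption, and the document offers nothing to support it. The conclusion rests on the inference that recruiters know the arm, and on taking the full explanation of objectives at its word.

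**What to change.** 1. **Recruitment Strategy:** replace purposive sampling with consecutive approach to every eligible caregiver at each clinic until the target is met. Keep a log of approached, eligible, declined and enrolled, by hospital.
2. **Phase 2 Overview and Allocation and Blinding:** state that only the group label is withheld, and describe the trial as open-label for participants with masked analysts.
3. **Allocation and Blinding:** keep arm and hospital as coded labels until the primary models have been run and locked. Hospital needs coding too, because it identifies the arm.
4. **Strengths and Limitations:** state that arm-aware selection and visible treatment limit internal validity, and that the self-rated scales are more exposed than the knowledge test.

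The cost is a screening log, wording changes and somewhat more approach effort; the available caseload is not stated and should be checked. The article says that Phase 2 had not started at submission. If recruitment has since begun, items 2 and 4 can still be done, item 3 can be done as long as analysis has not begun, and approach counts can be reported as far as they were kept.
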